### Sample size and recruitment

We calculated the sample size based on our primary outcome of HbA1c which is evaluated at baseline, 3 months, 6 months and 9 months. We assume a mean difference of 0.36%, a standard deviation of 1.5% [29], and an auto-correlation of 0.375 [30] between the repeated HbA1c measurements. The standard deviation of 1.5% was derived from data from the SingHealth Diabetes Registry, which showed the standard deviation of HbA1c for patients from polyclinics, hospitals and national specialty centres ranging from 1.4–1.5 from 2013–2019 [29]. Conservatively, we postulated that effect size of a complex intervention involving health coach and mobile app would result in a mean difference of 0.36% in HbA1c levels between the intervention and control groups. A meta-analysis has shown that the mean reduction in HbA1c is 0.41% for high quality studies involving mobile applications for Type 2 diabetes [31]. The auto-correlation of 0.375 between the repeated HbA1c measurements was assumed as it provided the most conservative (i.e. maximum) estimate of the sample size based on a repeated measurement study design with one-pre and three-post intervention measurements [30].

Based on a repeated measures study design [30] with one pre- and three post-intervention measurements, a minimum sample size of 125 per group, or 250 in total would have an 80% power to detect the hypothesised difference at a two-sided alpha of 5%. A total of 320 participants will be required after accounting for 20% attrition.

We will be advertising the study through posters and banners placed at polyclinic sites to ensure adequate enrolment to reach the target sample size of 320.

### Randomization and blinding process

Participants will be randomised to intervention or control group using a computer-generated randomization list provided by the trial biostatistician. We implemented stratified block randomization using randomly varying block sizes with recruitment site and duration of diabetes (<10 years or ≥10 years) as stratification factors based on a 1:1 allocation ratio. The cut-off of 10 years for duration of diabetes is supported by the data from previous studies [32, 33] and local SingHealth Diabetes Registry (mean disease duration ranging from 9.0–11.3 years from 2013 to 2019) [34].

Upon obtaining informed consent and enrolling a participant, the research coordinators at the polyclinic sites will contact a centralised research staff (who oversees the study progress but is not involved in patient recruitment) for the randomisation assignment.

The data analyst will be blinded to the assignment of interventions. It is not possible to blind study participants and care providers to the random assignment due to the nature of the intervention in this study.

### Statistical analyses

We will summarise participant’s characteristics using median (interquartile range) for non-normally distributed or mean (standard deviation) for normally distributed continuous variables respectively, and count and percentage for categorical variables. We will analyse the primary outcome of change in HbA1c over the 9 months follow-up, using a linear mixed model with adjustment for baseline HbA1c. A further model will be considered to explore whether the treatment effect on HbA1c varies with time, by including the treatment by time interaction, and adjusting for baseline systolic blood pressure and other potential confounders as appropriate via the mixed model.

We will use linear mixed model to account for within-individual correlation among measurements, and the sandwich estimator to obtain robust standard error estimates for secondary outcomes with repeated measurements (e.g., systolic blood pressure, quality of life, patient activation score). Pseudo maximum likelihood estimation method will be used for the parameter estimation. We will include intervention indicator and time factor as predictors, adjusting for the respective baseline covariates. For both the primary and secondary outcomes, alternative models such as mixed effect quantile regression may be considered if the model assumptions are violated.

All evaluations will be made using two-sided p-values at the 5% level of significance. Statistical analyses will be conducted based on the principle of intention-to-treat.

We will also conduct an economic evaluation from the health care system and societal perspectives. We will perform both cost-effectiveness analysis (i.e., cost of reduction in 1% in HbA1c) and cost-utility analysis (cost of reduction in 1 quality-adjusted life year saved).

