### Inclusion and exclusion criteria

Patients are recruited from three polyclinics in Singapore, which are public healthcare centres providing subsidised primary care. The trial inclusion criteria at the time of recruitment are:

(1) Aged 21 years and older,(2) Has a diagnosis of diabetes,(3) Haemoglobin A1c (HbA1c) ≥ 7.0% (most recent result),(4) Systolic blood pressure≥ 140 mmHg or diastolic blood pressure ≥ 90 mmHg on two or more prior visits, physician-diagnosed hypertension, or on antihypertensive medication,(5) Able to exercise physically,(6) Literate in English.

We will exclude patients who at the time of recruitment:

(1) Require aid with basic activities of daily living,(2) On bolus insulin,(3) Have upcoming major medical or surgical procedure during the trial,(4) Impaired cognitively [22].

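### The stated primary model leaves out the two randomisation stratification factors; adding them is a free, low-severity improvement that matters only if they predict HbA1c beyond baseline

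*Protocol article*

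**What the plan says.** In the protocol article, the section on randomisation and blinding describes stratified blocks of varying size, "with recruitment site and duration of diabetes (<10 years or ≥10 years) as stratification factors". The eligibility section gives the number of sites: "Patients are recruited from three polyclinics in Singapore". The design therefore has 3 × 2 = 6 strata.

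The section on statistical analyses names covariates for three sets of models:

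- **Primary HbA1c model:** "using a linear mixed model with adjustment for baseline HbA1c".
- **Further model**, which explores whether the effect changes over time: "adjusting for baseline systolic blood pressure and other potential confounders as appropriate via the mixed model".
- **Secondary outcomes with repeated measurements:** intervention, time and baseline covariates matched to each outcome, with sandwich standard errors.

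Neither site nor diabetes duration is named in any of the three. As written, they could enter only through the open-ended part of the further model or a broad reading of the secondary-model wording.

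**The concern.** Stratified blocks make the arms nearly equal on site and duration. If these factors are related to the outcome, that balance lowers the true variance of the treatment estimate. A model without them leaves their variation in the residual and computes its standard error as if allocation had not been stratified. The reported standard error is then larger than the true one, intervals are somewhat wide, the test rejects less often than its nominal 5%, and part of the precision gained by stratifying goes unused.

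The sandwich estimator planned for the secondary outcomes does not correct this. It allows for correlation within a participant but takes no account of the strata.

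At stake are efficiency and the match between design and analysis, not validity.

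**Working it through.** **Inputs from the protocol article (sample size section).** Difference 0.36, SD 1.5, auto-correlation 0.375, one pre- and three post-intervention measurements, two-sided 5%, 80% power, 125 per group. **Input not in the protocol:** R², the share of residual HbA1c variance that site and duration explain once baseline HbA1c is in the model. It is assumed to lie between 0 and 10%.

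**Step 1: the planned size.** For baseline-adjusted analysis of r = 3 post-intervention values:

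- Variance factor = (1 + (r − 1)ρ)/r − ρ² = (1 + 2 × 0.375)/3 − 0.375² = 0.5833 − 0.1406 = 0.4427.
- Effective SD = 1.5 × √0.4427 = 0.998.
- n per group = 2 × (1.960 + 0.842)² × 0.998² / 0.36² ≈ 121 (normal approximation), or 122 with the t distribution.

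The protocol states 125. At 125 per group, SE = 0.998 × √(2/125) = 0.1262, and 0.36/0.1262 = 2.85. Power is Φ(2.85 − 1.96) = 81.4% (81.1% with the t distribution). The stated size is thus essentially reproduced with no credit taken for stratification.

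**Step 2: effect of leaving the factors out.** Under stratified allocation the true variance of the estimate is multiplied by (1 − R²), while the model without the factors still reports the full variance. Hence:

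- SE overstatement = 1/√(1 − R²) − 1
- Type I error = 2 × Φ(−1.96/√(1 − R²))
- Power without the factors = Φ((2.85 − 1.96)/√(1 − R²))
- Power with the factors = Φ(2.85/√(1 − R²) − 1.96)

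| Assumed R² | SE too large by | Type I error | Power without factors | Power with factors | Points forgone |
|---|---|---|---|---|---|
| 0% | 0% | 5.0% | 81.4% | 81.4% | 0 |
| 1% | 0.5% | 4.9% | 81.5% | 81.8% | 0.3 |
| 2% | 1.0% | 4.8% | 81.6% | 82.1% | 0.5 |
| 5% | 2.6% | 4.4% | 82.0% | 83.3% | 1.3 |
| 10% | 5.4% | 3.9% | 82.6% | 85.2% | 2.6 |

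**Step 3: simulation check.** The set-up was stratified blocks over 3 sites × 2 duration groups, 250 participants, 4,000 runs per setting, and ANCOVA on the mean of the three follow-up values.

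| R² | Empirical SE, without / with | Model SE, without / with | Power, without / with | Null rejection, without / with |
|---|---|---|---|---|
| 0% | 0.1242 / 0.1243 | 0.1264 / 0.1264 | 81.1% / 81.1% | 5.7% / 5.6% |
| 5% | 0.1215 / 0.1214 | 0.1265 / 0.1232 | 81.3% / 82.8% | 4.4% / 4.7% |
| 10% | 0.1205 / 0.1204 | 0.1265 / 0.1200 | 81.5% / 84.0% | 3.7% / 4.6% |

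(SEs and power are from the runs with a true difference of 0.36; null rejection is from the runs with no difference.) The two estimates vary by practically the same amount. What differs is the reported standard error, so any loss comes from an overstated SE and not from a worse estimate.

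**Step 4: a rough gauge of R².** With a baseline slope of about 0.375, a lasting HbA1c difference D between strata leaves (1 − 0.375)D = 0.625D in the residual. Suppose duration alone carried the effect and the two groups were equal in size. Then R² ≈ (0.625D)²/(4 × 0.998²), so R² of 1, 5 and 10% needs D of about 0.32, 0.71 and 1.01 percentage points. Baseline adjustment therefore does not make the factors redundant, but the upper end of the table needs a sizeable lasting gap.

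**The case against.** The strongest reply is that this is a condensed article. It says the model adjusts for baseline HbA1c, not that it adjusts for nothing else, and the full covariate list may stand in a protocol or analysis plan that is not shown. That limits the point: nothing here shows that the factors will be excluded in the end. It does not remove it, because the article does name covariates for three sets of models, and the design factors are in none of them. For the secondary models the wording is plural and undefined, so there the factors can only be called unnamed.

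Several stronger readings are tempting, and the protocol does not support them:

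- **That the standard error is certainly too large and power is certainly lost.** This depends on R² given baseline HbA1c, for which no figure is given. At R² = 0 nothing is lost.
- **That the trial is underpowered for this reason.** The sample size takes no credit for stratification, and power at 125 per group is about 81% without the factors. What is forgone is an unplanned gain.
- **That the result would be biased or the false-positive rate raised.** The estimate is not biased, and any shift in type I error is downward.
- **That the factors were chosen because they predict HbA1c control.** The randomisation section justifies only the 10-year cut-off, from previous studies and the registry's mean disease duration. It gives no reason for stratifying by site.

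**Conclusion.** The point holds in a limited, conditional form. The stated covariates do not match the stratified randomisation. If site or duration predicts follow-up HbA1c beyond baseline, the primary model's standard error is overstated by 0.5 to 5.4% and about 0.3 to 2.6 points of power are forgone, for an assumed R² of 1 to 10%. At R² = 0 there is no cost. The omission and the direction of its effect are clear. The size rests on the assumed R², on complete data at 125 per group and on the equal-correlation structure of the protocol's own sample size. No size was worked out for the secondary outcomes, where only the mechanism carries over. This is a free improvement of low severity.

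**What to change.** In the section on statistical analyses, state that the primary HbA1c mixed model includes recruitment site (three levels) and diabetes-duration stratum (<10 or ≥10 years) as fixed effects alongside baseline HbA1c. State the same for the secondary-outcome mixed models, alongside the baseline value of each outcome. If leaving the factors out is deliberate, say so and give the reason.

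The cost is one sentence and three degrees of freedom (two for site, one for duration). Both factors must be known for every participant before allocation, so the change adds no data collection and no missing covariates. At R² = 0 the simulated power is the same with or without the factors. The wording should be settled before anyone responsible for the analysis sees comparative data, so that the choice cannot be read as data-driven.

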### Implementation

We will assess the impact and sustainability of interventions using the RE-AIM framework [35]. Data sources include qualitative focus groups and interviews with a purposive sample of participants and stakeholders, survey data, and electronic medical records. In addition, qualitative interviews will be conducted with a purposive sample of participants to collect their feedback on the EMPOWER app, health coaching and shared decision making interventions in promoting behavior change based on shared domains of the theoretical domain framework [36, 37] and social cognitive theory [38]. Specifically, we will focus on exploring knowledge, skills and reinforcement, self-efficacy, beliefs about consequences (outcome expectation), intention and goals, environmental context and social support/influences (S4 File: Sample interview questions for patients). These domains will assist in identifying cognitive, affective and social/environmental factors influencing behavioral change. In addition to patient interviews, interviews with healthcare professionals (clinician, health coach) and research coordinators will be conducted to elucidate implementation challenges and experiences (S5 File: Sample interview questions for other stakeholders). The details on data sources and parameters assessed for each RE-AIM dimension can be found in Table 2.

**Table 2 pone.0296338.t002:** Data sources and parameters assessed for RE-AIM dimensions.

RE-AIM Dimension	Data source	Parameters
Reach	Demographic data, administrative data, RCT survey data, interviews with stakeholders	Estimated number and percentage of patients with comorbid diabetes and hypertension approached Estimated number and percentage of patients eligible for the study Reasons for refusal to participate Number and percentage of dropouts, and reasons
Effectiveness	RCT survey data, EMR	Clinical measures before and after the intervention: HbA1c to target BP readings to target Long term complications (e.g., Major Adverse Cardiac Events, death, surgery, stroke, amputations, renal failure) Patient activation (Patient activation measure [26]) Physical activity (Wearable data) Medical Adherence (Voils DOSE-Nonadherence [27] and medication logging in EMPOWER app) Dietary changes (Diet logging in EMPOWER app) Quality of life (EQ-5D [28]) Length of stay, hospital-free days Direct healthcare cost, indirect healthcare cost
Adoption	Interviews with stakeholders	Interest of institutions and clinicians to adopt the interventions Proportion of patients expressed interest in continuing interaction with health coach Support from relevant partners and staff members
Implementation	Fidelity checks, RCT survey data, interviews with patients and stakeholders	Patient compliance to monitoring schedule Patient feedback on intervention (EMPOWER app, health coaching and shared decision making) Factors facilitate or impede implementation Adherence to protocol by health coach
Maintenance	Administrative data, Interviews with patients and stakeholders, survey data	Usage of EMPOWER app after completion of RCT Usage of smartwatch after completion of RCT Clinical outcomes at 3 and 6 months after completion of RCT Patients feedback on sustained usage of EMPOWER app and smartwatch

Abbreviation

BP: Blood pressure; EMR: Electronic medical records; HbA1c: Haemoglobin A1c; RCT: Randomised controlled trial

### Data management

We will secure the hardcopy survey data in locked storage spaces at the respective recruitment sites. Research coordinators will enter data into a secure web application [39, 40]. We will secure the EMPOWER app data and Fitbit data on a password-protected cloud, where only study team members will have access. We will retrieve data from the electronic medical records upon participant’s consent. The principal investigator will oversee data entry, data monitoring and audit procedures. Only the principal investigator and site principal investigators approved by the institutional review board will have access to the final trial dataset. The authors have access to information that could identify individual participants during and after data collection.

### Data monitoring

A data and safety monitoring board (DSMB) will ensure proper conduct of this trial and patient safety. At 6-month of completed follow up for 160 participants, the independent DSMB will conduct a planned monitoring of the unblinded effectiveness and safety data. All adverse events will be recorded.

## Discussion

This study will be the first to report on the effectiveness and implementation of complex intervention including personalised nudges driven by AI, health coaching and shared decision-making informed by behaviour change theory [41] for comorbid diabetes and hypertension management. Our study is conducted in an Asian healthcare setting, which will add much needed evidence to prior mHealth studies on chronic disease self-management that have been conducted primarily in the context of Western healthcare settings [42, 43]. Previous studies have demonstrated the importance of cultural adaptations of healthcare interventions to their effectiveness [44, 45]. The implementation of digitalisation and automation of nudging via mobile application, health coaching and shared decision-making in this study has the potential to alleviate time and resource constraints in primary care [9, 46, 47].

Our hybrid implementation-effectiveness study will provide valuable insights into a novel care model comprising mHealth and health coaching in the management of chronic diseases such as diabetes and hypertension. The evaluation of interventions using the RE-AIM framework [35] as well as feedback on the multi-component intervention (comprising EMPOWER app, health coaching and shared decision making) in promoting behavior change based on shared domains of theoretical domain framework [36, 37] and social cognitive theory [38] will generate findings on both impact and sustainability. Clinicians, researchers and policy makers will glean insights as to how cost-effective mHealth, health coaching and shared decision-making interventions can be scaled up and sustained among patients with comorbid diabetes and hypertension for behavioural change.
